### Baseline assessment

Baseline assessments will commence at the third visit, which will involve a muscle biopsy from the vastus lateralis, adipose tissue biopsies from subcutaneous abdominal tissue, and body composition assessment by dual X-ray absorptiometry (Monash Medical Centre Radiology Department). The final baseline visit will involve an intravenous glucose tolerance test and a hyperinsulinemic euglycemic clamp. Participants will complete validated questionnaires to assess self-reported sun exposure habits, physical activity (International Physical Activity Questionnaire) [38], knee and back pain, depression (Beck’s Depression Inventory) [39], and diet (3-day food record).

### Randomization

Following successful screening and baseline assessment, subjects will be randomized by a computerized randomization program to commence treatment with either vitamin D or placebo. This randomization will be done in blocks of four by sex and time of study entry (seasons) to ensure balance between the sexes in each test group and to control for the effect of seasonal change. Randomization of participants to the intervention or placebo groups will be completed by a researcher within our department (Monash Centre for Health Research and Implementation) who is not involved in the trial data collection, analysis, or reporting. This researcher will receive packaged supplements, produced by a clinical trials pharmacy, at Alfred Hospital. Capsules of vitamin D and placebo will be provided in clear containers and they will be identical and tasteless, to ensure that both participants and investigators are blinded to the treatment. To maximize compliance, participants will be provided with a calendar sheet highlighting the study period, so they can cross out each day as they go, and return the sheet along with the empty containers at the end of the study.

### Intervention

Following randomization, each participant will be given an initial first dose of 2,500 μg (100,000 IU) of vitamin D or an equivalent number of placebo tablets to be taken orally in front of researchers in the clinic. For those in the intervention group, this first dose is expected to elevate their serum concentration of 25(OH)D to 100 nmol/l within one week [10]. After the first dose, participants will take 100 μg/day (4,000 IU, four tablets) of vitamin D daily to keep their serum concentration of 25(OH)D at an optimal level. The daily dose selected is based on the amount required for repletion within a 3-month period [11], and is well below levels of intake associated with toxicity [40]. Participants on placebo will take four tablets daily of identical appearance. All participants will be instructed to consume four tablets daily, and otherwise maintain their usual daily activities.

### Follow-up visits

Participants will be scheduled for their follow-up visits during the last week of their treatment intake. All procedures performed during baseline assessment including blood pressure measurement, anthropometry, percutaneous muscle and adipose tissue biopsies, intravenous glucose tolerance testing, and glucose clamp will be repeated, except for the oral glucose tolerance test, as this is only performed initially to screen for diabetes. Participants will again be asked to fill out the same questionnaires and another 3-day food diary.

### Safety considerations

During the screening, baseline, and follow-up procedures, any medical conditions or abnormalities detected (except vitamin D status) will be promptly discussed with the participant by a qualified medical practitioner involved in the study. Where applicable, participants will be treated, referred, or advised to visit their general practitioner for follow-up. Individuals with frank vitamin D deficiency (<25 nmol/l) will not be included in the trial, as not treating these individuals would be unethical; hence, immediate treatment with vitamin D takes precedence. This severely deficient group will receive the same vitamin D supplementation and protocol (except randomization), and, along with their investigators, will remain blinded to maintain allocation concealment for this group. Results from these individuals will be analyzed separately from the trial. All participants will be informed of their screening blood test results after they have completed participation in the study, and they will be advised to visit their general practitioner to discuss strategies to increase or maintain their vitamin D levels, as well as improve their diabetes and cardiovascular risk profile.

### Ethics

This trial has received ethical approval from the Monash University Human Research Ethics Committee and Monash Health (protocol ID: CF13/3874 – 2013001988).

### Outcome measurements

The primary outcome measure in this trial is the difference (change) in insulin sensitivity between the vitamin D and placebo groups. Secondary outcome measures include changes in insulin secretion, weight, body mass index, waist, waist to hip ratio, resting systolic and diastolic blood pressure, lipid profile, and markers of inflammation, including IL-1β, IL-6, IL-8 and IL-10, CRP, TNFα, macrophage migration inhibitory factor, monocyte chemotactic protein-1, and NFκB activity. Measurement of insulin signaling in skeletal muscle and gene expression of inflammatory markers in adipose tissue will also be included as secondary outcome measures. Other outcome measures will include self-reported questionnaire data and nutrient analyses derived from dietary records.

### Data collection and analysis

#### Anthropometry

##### Body mass index

Using a digital scale (Tanita BWB-600, Australia) and stable stadiometer (Seca 206, Australia), body weight (kg) and height (m) will be measured, both at baseline and following the intervention period, during which participants will be lightly clothed and without shoes. These measurements will be converted to body mass index using the formula:$$ \mathrm{Body}\ \mathrm{mass}\ \mathrm{index} = \mathrm{Weight}\ \left(\mathrm{kg}\right)\ /\ \mathrm{Height}\ {\left(\mathrm{m}\right)}^2. $$

##### Waist to hip ratio

Central adiposity will be assessed in duplicate using a constant-tension tape for measuring waist and hip circumference. Waist circumference will be measured by a single experienced researcher at the midpoint between the upper iliac crest and the lowermost rib at the end of a normal expiration, while hip circumference will be determined at around the widest part of the buttocks. Waist to hip ratio will be calculated using the formula:$$ \mathrm{Waist}\ \mathrm{t}\mathrm{o}\ \mathrm{hip}\ \mathrm{ratio} = \mathrm{Waist}\ \mathrm{circumference}\ \left(\mathrm{cm}\right)\ /\ \mathrm{Hip}\ \mathrm{circumference}\ \left(\mathrm{cm}\right). $$

##### Body fat composition (dual X-ray absorptiometry)

Dual energy X-ray absorptiometry will be used to measure whole body fat composition. The fat tissue mass measured in this way consists of the sum of the fatty elements of all the soft tissue, not just adipose tissue, while the lean tissue mass reflects the sum of all chemical fat-free tissue components. Dual X-ray absorptiometry has been validated as an accurate, safe, and noninvasive method of measuring soft tissue body composition by region [41].

#### Metabolic measures

##### Oral glucose tolerance test

After a 10–12 hour overnight fast, participants will ingest 75 g of glucose over 2 min. Blood samples will be drawn at 0 and 120 minutes to analyze plasma glucose levels and determine diabetes status.

##### Percutaneous muscle and adipose tissue biopsy

Approximately 120 mg of skeletal muscle (vastus lateralis muscle) will be obtained by percutaneous muscle biopsy under local anaesthetic, immediately frozen and stored at −80 °C for later analysis. Adipose tissue (approximately 10 g) will be obtained by needle biopsy from the abdominal area, also under local anaesthetic, and will be immediately frozen and stored at −80 °C for later analysis.

##### Hyperinsulinemic euglycemic clamp

A euglycemic glucose clamp will be used to measure insulin sensitivity. After collecting baseline blood and plasma glucose levels at 0 min, the clamp will be initiated by an intravenous bolus injection of insulin (9 mU/kg). Insulin will then be constantly infused at a rate of 40 mU/(m^2^ min) for approximately 120 min into an arm vein, while glucose is variably infused to maintain euglycemia. Plasma glucose values will be monitored every 5 minutes during the clamp and the variable infusion rate of glucose will be adjusted to maintain blood glucose at a constant value of 5 mmol/l for at least 30 minutes.

##### Intravenous glucose tolerance test

Acute insulin secretory response will be measured using an intravenous glucose tolerance test. First, baseline blood will be collected at −10 and 0 min, after which 50 ml of 50 % glucose will be delivered intravenously over a 3 min period. Blood will then be collected for insulin concentration measurement at 3, 4, 5, 6, 8, 10, 15, 20, 25, and 30 min and glucose concentrations will be analyzed at each of these times, to determine insulin secretory response. This will be calculated as the average incremental plasma insulin level from the third to the fifth minute after the glucose bolus.

#### Cardiovascular measures

##### Blood pressure

Resting systolic and diastolic blood pressure and pulse rate will be measured using an automated oscillometric measurement system (Omron, Australia) after a 20-min rest. The average blood pressure derived from three measurements will be recorded.

##### Lipid profile

Lipid profile-related parameters to be measured include plasma total cholesterol, triglycerides, low-density and high-density lipoprotein cholesterol using a standard commercial enzymatic assay, a Beckman Coulter LX20PRO analyzer and SYNCHRON Systems lipid and multi calibrators (Beckman Coulter Diagnostics, Australia).

#### Inflammatory measures

##### Inflammatory markers

Plasma inflammatory markers (IL-1β, IL-6, IL-8 and IL-10, TNFα, macrophage migration inhibitory factor, and monocyte chemotactic protein-1) will be measured using a commercial automated chemiluminescent enzyme immunoassay analyzer (Immulite, Diagnostic Products Corporation, CA, USA), while plasma CRP will be analyzed via highly sensitive near infrared particle immunoassay rate methodology and a Beckman Coulter SYNCHRON LX system chemistry analyzer (Beckman Coulter Inc., Australia).

##### NFκB and Jun N-terminal protein kinase-1 activity

Nuclear extracts of white blood cells will be obtained and analyzed for the p50/p65 subunit of NFκB for their binding capacity for an NFκB consensus sequence (Active Motif, CA, USA). The bound subunits are sequentially incubated with specific antibodies to either the p50 or p65 subunit and then detected by their supershift on gel electrophoresis (Perkin Elmer, MA, USA). Activation of Jun N-terminal protein kinase-1 in the muscle and adipose tissue will be detected by immunochemistry and Western blotting, using antibodies from Cell Signaling Technology (MA, USA) and quantified using Quantity One imaging software (Bio-Rad Laboratories Inc., CA, USA).

#### Insulin signaling

We will measure changes in the expression and activation of important insulin signaling proteins, including the insulin receptor, insulin receptor substrate (IRS)-1 and 2, p85 subunit of phosphatidylinositol 3-kinase, and PKB/Akt, using Western blotting analysis, immunoprecipitation techniques, and commercially available phosphospecific antibodies (Santa Cruz Biotechnology, USA; Upstate Biotechnology, USA; Cell Signaling, MA, USA).

#### Gene expression

Gene expression of TNFα, IL-6, CRP, NFκB, and IKKβ in muscle and adipose tissue will be determined by real-time quantitative RT-PCR using the TaqMan system, based on real-time detection of accumulated fluorescence (ABI Prism 7700 sequence detection system; PE Biosystems, CA, USA). The protein concentration of all protein isolates will be determined using the bicinchoninic acid protein assay (Pierce Biotechnology Inc., IL, USA), according to the manufacturer’s instructions.

#### Other blood and tissue analyses

Other analyses include measurement of 25(OH)D concentration by direct competitive chemiluminescent immunoassay and a DiaSorin LIAISON Analyzer (DiaSorin Inc., USA) (CV 15 %); measurement of intact parathyroid hormone levels by an Access/DXI PTH assay, which is a paramagnetic particle chemiluminescent immunoassay for quantitative analysis (Beckman Coulter Inc., Australia); and measurement of insulin levels by Access/DXI ultrasensitive insulin assay, which is a simultaneous one-step immuno-enzymatic sandwich assay with CV levels of 7 %, 6.2 %, and 4.6 %, respectively (Beckman Coulter Inc., Australia). Serum concentrations of calcium, magnesium, and phosphate will be determined using automated colorimetric assays carried out on SYNCHRON LX and SYNCHRON DXC800® systems (Beckman Coulter Diagnostics, Australia), while plasma concentration of glucose will be determined using the SYNCHRON DXC800 and by an oxygen consumption rate method using a glucose oxygen electrode (Beckman Coulter Inc., Australia).

#### Self-reported measures

##### Nutrient analysis

Because some diets might be richer in vitamin D content than others, it was considered important to assess dietary practices of the study participants. The participants will be asked not to change their dietary habits during the study, and to complete a 3-day food diary, which will provide a snapshot of the types of food consumed by the participants when they entered the study as well as at follow-up, to ensure no major change in diet. These 3-day records will be analyzed with Food Works Professional 2007 (Xyris Software, Qld), a nutrient analysis program based on Australian food composition tables. Where possible, Australian data on the vitamin D content of foods will be used in the analyses [42]. Where Australian data are unavailable, a vitamin D database that we have recently compiled from UK, US, and European food composition tables will be employed.

##### Sun exposure questionnaire

Skin colour, owing to different quantities and compositions of melanin, affects the cutaneous photochemical synthesis of vitamin D [43]. Similarly, season and latitude influence vitamin D production in the body [43]. To take these into account, we have included a sun exposure questionnaire. Skin characteristics will be measured by grading hair colour (ten-point visual scale), eye colour, and reaction to sun exposure (four-point scale: *never* to *always* burn) [44]. Participants will be asked to estimate their average hours of sun exposure on a usual working day and on a nonworking day, to indicate how often sunscreen was used and its sun protection factor, and to describe the degree of clothing worn when outside during the summer and winter seasons. The description of clothing worn will then be used to determine the fraction of body surface area exposed to sunlight [45] and to calculate a sun index [45]:$$ \mathrm{Sun}\ \mathrm{index} = \mathrm{Hours}\ \mathrm{of}\ \mathrm{sun}\ \mathrm{exposure}\ \mathrm{per}\ \mathrm{week} \times \mathrm{Fraction}\ \mathrm{of}\ \mathrm{body}\ \mathrm{surface}\ \mathrm{area}\ \mathrm{exposed} $$

##### International Physical Activity Questionnaire

The aim of the validated International Physical Activity Questionnaire is to establish the kinds of physical activity people engage in during their average day [38]. We opted to include the short version to make it more timely and convenient for participants, given that its purpose is to determine any change in physical activity that could influence our study outcomes. This version refers to the preceding 7 days and asks participants to report the number of days, and of hours and minutes, spent on vigorous activity, such as aerobics, or moderate activity, such as carrying light loads [38]. It also asks about the number of days, and of hours and minutes, participants walked for at least 10 minutes and how much time they spent sitting for any activity (work, travel, leisure, and so on) over the preceding 7 days.

Secondary outcome information derived from this short survey might provide some insight into whether different activity levels might be correlated with different vitamin D levels. While it is unlikely that we would reach any solid conclusions from this particular dataset, it might serve as a potential starting point for further, more comprehensive research in future.

##### Beck’s Depression Inventory

Beck’s Depression Inventory (2nd edition) is one of the most commonly used and validated diagnostic tools for depression and for determining its severity in diverse population groups, including different ethnicities and age groups, and in those with and without histories of depressive disorders or psychological distress [46, 47]. The influence of vitamin D deficiency on the likelihood of reporting depressive symptoms is currently unknown [48, 49], thus we have chosen to employ this questionnaire as a reliable tool for examining this relationship at baseline, and to assess whether depressive symptom reporting might change following vitamin D supplementation.

In this questionnaire, participants will be asked to report the frequency by which they have experienced such feelings as sadness, discouragement, dissatisfaction, guilt, indecisiveness, irritation, and suicidal thoughts, over the past 7 days. There are 21 multiple choice items in total, each with four possible responses ranging from a score of 0 to 3 [39, 50]. The scores for all 21 items are tallied to reach a total score between 0 and 63, with higher scores indicating more severe levels of depression.

##### Knee and back pain questionnaire

There has been a fair amount of evidence showing an association between circulating 25(OH)D concentrations and certain bone health outcomes, including osteoporosis, rickets, falls and fractures, and osteoarthritis [51, 52, 30]. However, research is lacking in relation to vitamin D and self-reported musculoskeletal pain. As such, we have added the knee and back pain questionnaire in an attempt to establish whether vitamin D supplementation might improve scores on self-reported pain scales and therefore prove useful for the treatment of high-risk individuals, such as older people and overweight or obese individuals. This questionnaire will collect information from participants regarding the amount of pain they currently experience in their dominant knee during certain activities, such as walking or standing, the duration in which they have experienced back pain, and the intensity of any back pain encountered within the past 6 months.

#### Statistical analysis

All analyses will be conducted according to the intention to treat principle. Baseline patient characteristics will be assessed using Student’s *t* test for continuous variables and the chi-squared test for categorical variables, to check for any imbalance between the two groups. Distributional assumptions will be checked and continuous variables will be transformed if normality is violated. Baseline and within-group differences will be assessed using paired Student’s *t* tests for both primary and secondary outcome measures. The effects of the intervention on the outcomes (between-group differences) at 16 weeks will be analyzed using changes in outcome variables and linear regression. Here, the variable of interest at 16 weeks will be the outcome variable minus baseline variable, which will be additionally adjusted for baseline values. Using linear regression, pre-specified subgroups, such as age categories, sex, and body mass index will be assessed for effect modification on anthropometric, metabolic, and cardiovascular outcomes.

A separate analysis will be conducted for the severely vitamin D deficient group, who will undergo a nonrandomized mandatory treatment with vitamin D supplementation as per protocol. A within-subject analysis on primary and secondary outcome measures using paired *t* tests will be conducted on this group.

All analyses will be performed using Stata statistical software. All tests will be two-sided and *P* values of less than 0.05 will be considered statistically significant.

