## Methods/Design

### Study design and setting

This study is a parallel-group randomized placebo-controlled trial. The study design is presented in Fig. 1. Fifty overweight but otherwise healthy normoglycaemic adults aged between 18 and 60 years, and with serum concentrations of 25(OH)D between 25 and 50 nmol/l on screening will be enrolled. Participants will be randomized to receive either placebo or vitamin D supplementation (25 participants in each arm) for 16 weeks, with a goal of achieving optimal 25(OH)D levels of approximately 100 nmol/l. Those with severe deficiency (serum 25(OH)D levels below 25 nmol/l) will not be included in the current trial but will be allocated to a nonrandomized mandatory treatment group and studied before and after supplementation. Overweight and obese subjects will be selected for this study, as they are generally more insulin resistant and more sedentary, and have higher levels of inflammatory markers and lower levels of vitamin D, all of which are factors that increase the risk of type 2 diabetes [34, 35]. Participants will be sought out via several advertising strategies, including posters, flyers, newspapers, and email newsletters at Monash University and Monash Medical Centre in Melbourne, Australia, and via online advertising avenues, including social media and popular community websites. Interested participants will be informed that their participation is voluntary and that they can withdraw at any time, and they will also be asked to read the details of the study provided in an information pack. Once all concerns and questions have been addressed, participants will be asked to sign an informed consent form prior to commencing any tests.

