### Sample size calculation

Based on data from a similar healthy cohort of overweight or obese subjects in our metabolic laboratory, with a mean (standard deviation) insulin-mediated glucose uptake value of 8.1 (2.0) mg glucose per kg per minute, a sample size of 25 completing each arm is required to detect a 20 % change in insulin-mediated glucose uptake between treatment group and placebo. The 20 % increase is based on results from a study indicating the effect of vitamin D supplementation in subjects with diabetes using a comparable insulin sensitivity measurement technique and 4 weeks’ treatment [36]. Based on a type I error of 0.05 (two-tail) and a type II error of 0.20 (power = 80 %), we would require 50 participants to complete the trial.

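### Baseline significance tests at 25 per arm cannot show whether the arms are balanced; describe baseline instead and fix a short covariate set in advance (minor)

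*Protocol article*

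**What the plan says.** The Statistical analysis section of the protocol article plans baseline comparisons between the arms and gives their purpose: "Baseline patient characteristics will be assessed using Student’s *t* test for continuous variables and the chi-squared test for categorical variables, to check for any imbalance". The same section sets one threshold for everything: "All tests will be two-sided and *P* values of less than 0.05 will be considered statistically significant". It gives no criterion for the size of an imbalance.

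The between-group analysis is a linear regression of the change at 16 weeks, adjusted for the baseline value of the outcome. No other covariate is named for that model. Age, sex and BMI appear only as subgroup variables: "pre-specified subgroups, such as age categories, sex, and body mass index will be assessed for effect modification".

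Under Randomization, "subjects will be randomized by a computerized randomization program to commence treatment with either vitamin D or placebo", in blocks of four by sex and season of entry. The planned size is "25 participants in each arm", and the Sample size calculation asks for that number to complete. Methodological considerations lists, as a strength, the use of questionnaires to control for diet, physical activity, sun exposure and seasonality.

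**The concern.** The test does not answer the question put to it, for two reasons.

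- **The null is true by design.** When allocation is properly randomized, any baseline difference is due to chance. A baseline test then flags about 5% of variables whatever happened, and a flag says nothing about whether the difference matters.
- **The test is insensitive at this size.** The effect of an imbalance on the result depends on its size multiplied by the covariate's association with the outcome. The P value measures neither, and with 25 per arm sizeable differences stay above 0.05.

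At stake is how the primary estimate is read. If a prognostic covariate outside the model differs by chance, the estimate in that sample is shifted, and the planned check may show nothing. Conversely, with many baseline variables some will be flagged by chance, which invites covariates chosen after the fact.

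**Working it through.** **Inputs.** From the protocol: 25 per arm, two-sided 0.05, mean 8.1 and SD 2.0 mg/kg/min for insulin-mediated glucose uptake, and a target difference of 20%. Assumed: correlations of 0.3 to 0.5 between an omitted covariate and the change given baseline, and 15 independent baseline variables. The protocol gives neither.

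**The plan's own figure.** Target = 0.20 × 8.1 = 1.62 mg/kg/min, and 1.62 / 2.0 = 0.81 SD. An exact two-sample t calculation gives 24.92, so 25 per arm, with 80.1% power. The stated sample size is reproduced.

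**What the baseline t test flags.** The standard error of a difference in SD units is √(2/25) = 0.283. With t(0.975, 48 df) = 2.011, the threshold is 2.011 × 0.283 = 0.569 SD. An observed 0.5 SD gives t = 0.5 / 0.283 = 1.77 and P = 0.083.

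**What the chi-squared test flags.** Starting from 5, 8, 10 or 12 of 25 in one arm, the smallest gap reaching P<0.05 (uncorrected) is 7 participants, or 28 percentage points; for example, 8/25 against 15/25 gives P = 0.047.

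**How often this arises, per continuous covariate.**
- Imbalance above 0.3 SD: probability 0.294. Less the 0.05 that is flagged, 0.244 goes unflagged.
- Imbalance above 0.5 SD: probability 0.083. Less 0.05, about 0.033 goes unflagged.
- At least one chance flag among 15 variables: 1 − 0.95^15 = 0.54.

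**Shift in one realised sample.** For a covariate outside the model, the shift is roughly correlation × imbalance. At the threshold of 0.569 SD:
- correlation 0.3: 0.17 SD, or 0.34 mg/kg/min at SD 2.0, which is 21% of 1.62;
- correlation 0.5: 0.28 SD, or 0.57 mg/kg/min, which is 35% of 1.62.

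**The baseline value of the outcome.** In a null simulation with baseline imbalance between 0.40 and 0.57 SD, and baseline–follow-up correlation of 0.5 or 0.7, the planned baseline-adjusted change model had a mean bias of 0.005 and 0.003 SD. A raw 16-week comparison had 0.24 and 0.33 SD. The planned model removes this source.

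**Other covariates: error rates.** Simulation with 25 per arm and a model of arm plus baseline outcome, for correlations 0.3 / 0.4 / 0.5:

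| Situation | Type I error | Power at 0.81 SD |
|---|---|---|
| All samples the baseline test does not flag | 0.045 / 0.043 / 0.041 | 0.80 / 0.80 / 0.80 |
| Imbalance fixed at 0.5 SD, against vitamin D | about 0.07 / 0.08–0.09 / 0.10 | 0.61 / 0.54 / 0.50 |
| Same imbalance, covariate in the model | 0.046–0.052 | 0.80 / 0.83 / 0.87 |

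With the 0.5 SD imbalance in favour of vitamin D, power without the covariate is 0.92 / 0.94 / 0.97.

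**Cost and gain of adding two covariates, over all randomizations.** If neither predicts the change, power goes from about 79% to 77%. If one has a correlation of 0.3 to 0.5, power rises by about 1 to 9 points.

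**The case against.** The strongest reply is that nothing in the analysis depends on these tests. A reader might infer that the arms will be declared comparable when P>0.05, or that adjustment is withheld when nothing is flagged. The protocol says neither. The regression is the same whatever the baseline tests show, so deleting them changes no estimate. This stands.

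A reader might also infer that prognostic imbalance in general goes uncorrected. That is not supported either. The baseline value of each outcome, usually the strongest predictor, is always adjusted, and sex and season are balanced by stratified blocks. Only other covariates are left: age, BMI, baseline 25(OH)D, diet, activity and sun exposure. This also stands.

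A third tempting reading is that the false-positive rate is raised or power is sharply cut. The figures of 7–10% and 50–61% hold only for a realised imbalance of 0.5 SD, with the power figures requiring the adverse direction. They also rest on assumed correlations, and naming age and BMI as effect modifiers does not show that they are prognostic. An unflagged imbalance above 0.5 SD has a probability of about 3% per covariate, and half of those run in the adverse direction. Over all unflagged samples, type I error is just under 5% and power is the planned 80%.

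Finally, a full covariate list is often left to the statistical analysis plan, which is not shown. Its absence from the article is therefore not itself a fault. What does not fall away is that the article chooses a test for a purpose the test cannot serve.

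**Conclusion.** The concern holds in a narrow form, and it is minor. The planned baseline t and chi-squared tests are uninformative under randomization, and with 25 per arm they do not flag observed differences below about 0.57 SD. The threshold assumes all 25 per arm are measured and rests on no other assumption.

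The consequence is limited to prognostic covariates other than the baseline outcome, sex and season. For these, chance imbalance means some lost precision and a possible shift in the realised sample. At the flagging threshold the shift is 0.17 to 0.28 SD if the correlation with the change is 0.3 to 0.5, and smaller if the correlation is lower. The overall type I error is not inflated, and the document does not support a claim that it is.

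**What to change.** In the Statistical analysis section:

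1. Replace the baseline t and chi-squared tests with descriptive summaries by arm: mean (SD) or n (%), with standardized differences if a measure of size is wanted.
2. Name a short covariate set for the primary between-group regression and keep it whatever imbalance is observed: the baseline outcome value, the randomization strata (sex and season), and baseline age and BMI as continuous variables.

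This is a change of wording, to be made before unblinding. It needs no new participants or measurements, since these variables are already collected. The cost is a few residual degrees of freedom. Arm, baseline outcome and intercept leave 50 − 3 = 47; age and BMI take 2, leaving 45; sex takes 1 and season 3 if coded in four categories, leaving 41. For age and BMI the cost is about 2 points of power if they do not predict the change. If one correlates 0.3 to 0.5 with the change, power rises instead, by about 1 to 9 points.
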